### Secondary Analyses

Random effects models will be used to compare the annual rate of change in the absolute CD4 cell count, the annual rate of change in the CD4 cell count percentage, and the median log_10 _HIV viral load between study arms. The rate of drug-related adverse events per year of follow-up, the number of episodes of HSV reactivations per year occurring at any anatomic site, the proportion of microbiologically confirmed flares of HSV during the trial that are caused by laboratory-confirmed acyclovir-resistant HSV, and the median overall quality of life score [84] at each 6-monthly time point will be compared between groups using Wilcoxon rank sum tests. All analyses will be by intention to treat, meaning that all participants will be analysed in the groups to which they were randomized.

Efforts to ensure that the CD4 and other trial data are well collected include biannual investigator meetings to review study procedures, regular site monitoring visits, and electronic data checks at the CTN National Data Centre. Because the analyses on rates of change in CD4 will only include CD4 counts prior to HAART initiation, the usual problem in HIV clinical trials of missing data among patients doing poorly clinically and dropping out of the trial is not anticipated to be an issue. Patients doing poorly clinically will reach the primary outcome, and it is only their CD4 counts before this time that will be included in the analysis.

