### Eligibility Criteria

Individuals will be eligible for the trial if they meet the following inclusion criteria:

• adult (aged 18 years or older or as per Local/Provincial Guidelines)

• documented HIV-1 infection (determined by EIA and Western blot)

• documented HSV-2 seropositivity (determined by ELISA during screening; see below)

• no use of chronic anti-HSV therapy for the past 6 months, and not anticipated to require chronic anti-HSV therapy during the study

• antiretroviral naïve (no more than 14 days of total prior ARV exposure)

• CD4 count within the 400-900 cells/mm^3 ^range (inclusive) on two consecutive occasions, with at least one measurement within 4 weeks of initiating trial

• does not meet recommendations for initiating ARV therapy according to current guidelines[57,58]

Chronic anti-HSV therapy refers to the regular, daily use of medications with anti-HSV activity (such as acyclovir, valacyclovir, famciclovir, ganciclovir, valganciclovir, cidofovir, foscarnet). It does not refer to the episodic use of short courses of these medications for treatment of isolated HSV flares for a few days at a time.

The exclusion criteria for this study are as follows:

• pregnancy or actively planning to become pregnant

• receiving chemotherapy, chronic steroid therapy or other immunomodulatory medications (e.g. interferon, azathioprine, methotrexate, TNF-alpha antagonists, etc.)

• Estimated creatinine clearance < 30 mL/min

• Other medical condition likely to cause death within 24 months

• Enrolled in a therapeutic vaccine or immunotherapy trial

• Enrolled in another trial investigating the impact of another intervention on HIV disease progression

• HIV elite controller (EC), phenotypically defined here as documented duration of HIV infection of ≥5 years, a persistent CD4 cell count ≥500 cells/mm^3^, and a persistent plasma HIV viral load of < 1000 copies/mL in the absence of antiretroviral therapy[3,59-61]

A stringent, empiric definition of the EC phenotype will be used because previous reports have primarily characterized ECs on the basis of genetic and immune markers beyond the means of this study[3,59-61]. The heterogeneity of CD4 counts and viral loads in ECs implies that a more permissive definition may overlap considerably with the general HIV-infected population and risk introducing a selection bias.

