The secondary outcome measures to be compared between the two treatment groups include:

• Annual rate of change in CD4 count, calculated as the slope of participants' CD4 count change/time

• Annual rate of change in the CD4 cell count percentage, calculated as the slope of the participants' CD4 count percentage change over time

• Log_10 _plasma HIV viral load at 12, 24 and 36 months of follow-up

• Treatment-emergent adverse events and laboratory abnormalities (CBC, plasma creatinine)

• Frequency of episodes of symptomatic HSV reactivation at any anatomic site

• Proportion of microbiologically confirmed flares of HSV during the trial that are caused by laboratory-confirmed acyclovir-resistant HSV

• Overall quality of life as measured by the MOS-HIV questionnaire at each 6-monthly time point.

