### Duration of Study Participation

Study visits will occur every 3 months over 2 years of participant accrual and 3 years of follow-up. Once enrolled, participants will enter the follow-up period during which they will be treated with either valacyclovir or placebo, and undergo follow-up visits every 3 months. Follow-up for an individual participant will continue until the end of the 5-year study period unless the primary endpoint is reached first. This means that all participants will be followed until the 5-year trial ends, unless they reach a primary endpoint first.

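### MOS-HIV is compared by rank tests on raw visit scores that cannot use the baseline score, and no baseline term is stated for viral load: a minor, nearly free gain in precision is left unused

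*Protocol article*

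**What the plan says.** Outcome Measures defines the two CD4 outcomes as slopes within a participant, but defines the other two longitudinal outcomes as levels. Viral load is the log10 value of "plasma HIV viral load at 12, 24 and 36 months of follow-up". Quality of life is "Overall quality of life as measured by the MOS-HIV questionnaire at each 6-monthly time point".

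Secondary Analyses then assigns the methods. Random effects models are used for the CD4 slopes "and the median log_10 _HIV viral load between study arms", and no model terms are listed. For quality of life, the median score "at each 6-monthly time point will be compared between groups using Wilcoxon rank sum tests".

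Two other statements bear on the point. Under Duration of Study Participation, "all participants will be followed until the 5-year trial ends, unless they reach a primary endpoint first", so later visits contain only participants who are still endpoint-free. Under Eligibility Criteria, the elite-controller exclusion refers to "a persistent plasma HIV viral load of < 1000 copies/mL in the absence of antiretroviral therapy", which implies that viral load is known at entry. The article does not state whether MOS-HIV is taken at entry.

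**The concern.** A participant's follow-up value of either measure is partly predicted by the entry value. The Background and the sample size justification describe untreated viral load as a set point, so the link should be fairly strong there. An analysis that ignores the entry value leaves this predictable between-person variation in the error term.

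For MOS-HIV, the named test fixes that choice: a two-sample rank sum test on raw scores has no place for a covariate. For viral load, the model could carry baseline, but the text does not say that it does. The stated target is also a median, whereas an ordinary linear random effects model estimates a mean difference.

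There is a second strand. The Background calls viral load the major predictor of progression, and follow-up stops at the endpoint. If valacyclovir slows progression, the arms lose participants at different rates, and those left at 24 and 36 months may differ in baseline viral load. Conditioning on baseline would remove that part of the difference.

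**Working it through.** The plan gives no SD, correlation, precision or power for either outcome, so there is no figure of its own to reproduce. Every SD, correlation and retention value below is an assumption.

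**1. MOS-HIV, one visit.** Linear adjustment for baseline multiplies the variance of the arm difference by 1 − r², where r is the baseline/follow-up correlation. This is a normal-theory result and only a guide for a rank test.

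| r | variance reduction r² |
|---|---|
| 0.3 | 9% |
| 0.5 | 25% |
| 0.6 | 36% |

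**2. Numbers observed for viral load.** From Sample Size Calculation: 240 per arm, times to endpoint of 2 and 2.75 years (read here as exponential medians), and 25% lost over three years. Assumed retention is 92%, 83% and 75% at 12, 24 and 36 months. Then n = 240 × 0.5^(t/median) × retention.

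| Month | Endpoint-free, placebo vs valacyclovir | Observed n |
|---|---|---|
| 12 | 71% vs 78% | 156 vs 172 |
| 24 | 50% vs 60% | 100 vs 120 |
| 36 | 35% vs 47% | 64 vs 85 |

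If 2 and 2.75 years were means instead, fewer participants would remain and all intervals would be wider.

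**3. Viral load, pooled model.** Generalised least squares with visit effects, one common arm difference, exchangeable correlation r, participants leaving for good once they leave, and SD 0.8. Without baseline, the covariance over a participant's k observed visits is SD²[(1 − r)I + rJ], where I is the k × k identity matrix and J a matrix of ones. With baseline as covariate, SD²r²J is subtracted.

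| r | Half-width unadjusted | Half-width adjusted |
|---|---|---|
| 0.5 | 0.152 | 0.124 |
| 0.6 | 0.157 | 0.116 |
| 0.7 | 0.162 | 0.105 |
| 0.8 | 0.166 | 0.090 |

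The variance reduction is about 34% at r = 0.5 (1 − (0.124/0.152)² = 0.33 from the rounded values) and 71% at r = 0.8 (1 − (0.090/0.166)² = 0.71). Unadjusted power for 0.33 log10, the low end of the protocol's range, is already 97–99% at SD 0.8 and 88–93% at SD 1.0. For the planned 0.5 log10 at SD 0.8 it exceeds 99.9%.

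**4. Viral load, 36 months tested alone.** SE = 0.8 × √(1/64 + 1/85) = 0.132, so the half-width is 1.96 × 0.132 = 0.26. Power is 70% for 0.33 log10 and 96% for 0.5 log10. Multiplying the SE by √(1 − r²) gives half-widths of 0.21 (r = 0.6) to 0.16 (r = 0.8) and power for 0.33 of 87% to 99%.

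**5. Selection.** Simulation of the 24-month comparison among endpoint-free participants: 240 per arm, hazard ratio 2/2.75 = 0.727, SD 0.8, true effect −0.25 log10, and an assumed log hazard of +0.5 per SD of baseline viral load.

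| r | Raw difference (SE) | Baseline-adjusted (SE) |
|---|---|---|
| 0.5 | −0.217 (0.099) | −0.250 (0.087) |
| 0.7 | −0.206 (0.096) | −0.250 (0.070) |
| 0.8 | −0.200 (0.096) | −0.250 (0.060) |

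The remaining valacyclovir group had a baseline about 0.06 log10 higher, which shrinks the raw effect toward zero. With no effect on viral load and hazard ratio 1, both estimates centred on zero. Adjustment restores the true value fully only because the simulated hazard depends on nothing but arm and baseline.

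**The case against.** The strongest reply concerns viral load. A random effects model can carry baseline as a covariate or as a response, and a condensed article commonly leaves the terms of a secondary model to the analysis plan, which is not shown. A reader might infer that viral load will be analysed without adjustment. The text does not support that: adjustment is unstated, not ruled out.

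A reader might also take the 70% power at 36 months as the power of the planned analysis. It belongs to a separate test at the thinnest visit and the smallest effect in the protocol's range. A model that pools the three visits has high power without adjustment.

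Selection might be read as a route to a spurious benefit. It arises only if the drug alters progression, and in the simulation it ran toward no difference. A likelihood-based random effects model that includes earlier values from participants who later leave handles part of it already.

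Mean versus median is close to a wording point, since the two coincide if log10 values are roughly symmetric.

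These replies largely stand. They do not reach MOS-HIV, where the named test itself excludes baseline. Even there, under randomisation the Wilcoxon test is valid when there is no effect, so the loss is one of efficiency.

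**Conclusion.** The point holds as a minor improvement to two secondary analyses. It is firmest for MOS-HIV: the stated test cannot use baseline, and the variance reduction forgone is about 9% to 36% per visit at an assumed correlation of 0.3 to 0.6, provided that an entry score exists.

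For viral load, the point is that the baseline term should be stated. The gain is a pooled half-width of 0.09–0.12 instead of 0.15–0.17 log10 (assumed SD 0.8, correlation 0.5–0.8, median reading of the times to endpoint, one common arm effect), plus removal of the selection that baseline carries.

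A broader claim, that a third to a half or more of the precision is lost in both outcomes, is not supported. For a single visit it needs a correlation of about 0.58 or higher (0.58² ≈ 0.33; 0.71² ≈ 0.50), and the documents give none. The primary analysis is untouched.

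**What to change.** **MOS-HIV:** replace the visit-by-visit rank sum tests on raw scores with a repeated-measures model of the score on arm, visit and arm-by-visit, with baseline score as covariate. If scores are markedly skewed, use a rank-based test that adjusts for baseline. Confirm that MOS-HIV is collected at entry.

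**Viral load:** state that the random effects model includes baseline log10 viral load, either as a covariate or as a response with arm means constrained equal at baseline. Report a mean log10 difference with its interval in place of a median.

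**Cost:** analysis wording only, settled before unblinding. No extra participants or visits are needed. Viral load at entry is implied by the eligibility criteria; an entry MOS-HIV is an assumption, and if none is taken the MOS-HIV change is not available for participants already enrolled.

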These results bolster interest in the VALIDATE trial, which is addressing related but complementary issues. First, given the conduct of the Partners trial in resource-limited settings, it remains important to study the impact of HSV-2 suppression in co-infected patients from industrialized and middle-income countries. The endpoint of the Partners trial represented a stage of disease that can be avoided in settings where the standard of care is to offer HAART earlier; it is encouraging, therefore, that an exploratory analysis from the Partners trial demonstrated a delay in achieving CD4 < 350 cells/mm^3 ^from acyclovir as well (HR = 0.81, 95%CI 0.71-0.93, p = 0.002). Further, rates of CD4 count decline may be different in Sub-Saharan Africa due to the effects of nutritional status, heightened levels of immune activation (for example, as a result of co- or intercurrent infections), and HIV clade[46-49]. The predominant clades in Sub-Saharan Africa (A, D and C) differ from those in most industrialized countries (B and some others) and in South America (B but some F, C and recombinants)[50,51]. In addition, it should be noted that disease progression was a secondary endpoint of the Partners trial, which was primarily designed to study the impact of HSV-2 suppression on HIV transmission. Finally, VALIDATE is employing valacyclovir instead of acyclovir for HSV-2 suppression, and the dose of 500 mg twice daily has been demonstrated to achieve excellent herpes suppression in clinical trials of HIV, HSV-2 co-infected adults[41,42]. Valacyclovir is the pro-drug of acyclovir, and may offer advantages over acyclovir owing to an improved bioavailability (54.5% versus 15-30%) and lower pill burden[52].

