### Study Objectives

The primary objective of this trial is to compare the time from enrolment to the primary endpoint of either a CD4 cell count ≤ 350 cells/mm^3 ^measured on two consecutive occasions at least 1 month apart, or initiation of HAART for any reason, between adults with both stable untreated HIV and HSV-2 co-infection who are randomized to valacyclovir compared to those randomized to placebo.

Secondary objectives are as follows:

• To compare the annual rate of change in the absolute CD4 cell count between study arms.

• To compare the annual rate of change in the CD4 cell count percentage between study arms.

• To compare the median log_10 _HIV viral load between study arms.

• To compare the rate of drug-related adverse events between study arms.

• To compare the median frequency of HSV reactivations per year between study arms.

• To compare the rate of acyclovir-resistant HSV between study arms.

• To compare quality of life between study arms.

A substudy will characterize plasma markers of inflammation in this cohort of HAART-naive HIV-infected patients and compare the levels of these markers between study arms.

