### Study Hypotheses

The primary hypothesis of the trial is that valacyclovir 500 mg orally twice daily will delay the time until HAART is initiated among adults co-infected by stable untreated HIV and HSV type 2 co-infection. The secondary hypotheses are that valacyclovir 500 mg orally twice daily is associated with a slower rate of change in both the absolute CD4 cell count and the CD4 cell count percentage, a lower median log_10 _HIV viral load, a similar rate of drug-related adverse events, a lower frequency of HSV reactivations, a similar rate of acyclovir-resistant HSV, and improvements in quality of life compared with placebo.

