### Management of symptomatic herpes during the trial

If a clinical reactivation of herpes symptoms occurs during the trial, participants are instructed to continue their study drug, present for clinical assessment, have samples taken to attempt microbiologic confirmation of the diagnosis where resources permit, and consider optional open-label treatment. Although participants in the treatment arm may thus receive a total valacyclovir dose of up to 3 g per day for 5 days, this quantity remains well within the safe therapeutic window of this drug. Of note, the occurrence of herpes flares in a study participant does not in itself unblind the study, because a small proportion of individuals taking chronic suppressive anti-HSV medications can experience herpes reactivations. If HSV resistance is suspected, specimens will be tested for acyclovir resistance using a plaque reduction assay[69].

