Nine months is a clinically important difference in the time for HIV-infected patients to delay initiation of lifelong HAART. During this time, patients could avoid the costs, toxicity risks, and resistance risks of ARVs. Because typical HAART regimens can cost $1200 per month compared with only $150 per month for valacyclovir, this strategy could result in an annual net savings of nearly $10000 per patient based on medication costs alone. Further, although the toxicity profile of current ARVs is significantly better than in earlier years of the HIV epidemic, long-term toxicities remain unknown because most of the agents in current use were approved within the last 5-10 years. The ARV resistance risks to be avoided are also considerable; in clinical trials evaluating efavirenz-based HAART regimens, the current 'gold standard' for first-line ARV therapy, 30-70% of the 15-20% patients experiencing virologic failure at one year have evidence of resistance to the NNRTI class of drugs, effectively eliminating the potential for using standard agents in this class thereafter[73-77]. Delaying HAART also provides time for patients to prepare psychologically for starting HAART, which is an important predictor of subsequent adherence[78,79]. Nine months is also the time between 3 quarterly appointments, allowing ample time for clinician and patient to prepare for HAART. Finally, although there is theoretical risk of developing drug-resistant HSV with chronic valacyclovir, this risk is minimal even in immunocompromised patients. Resistance rates have stayed stable at 5-6% despite increasing population exposure to related drugs over 2 decades, perhaps because it imposes a fitness cost on the virus[15,80-83]. Resistant HSV is occasionally seen in advanced HIV patients with persistent lesions despite therapy, not in asymptomatic shedding. For safety, those with frequent recurrences unresponsive to therapy during the trial will have their viral isolates tested for resistance.

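### Acyclovir resistance is compared only as a share of confirmed flares, a denominator that valacyclovir is expected to shrink; a comparison over all randomised participants should lead

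*Protocol article*

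**What the plan says.** Study Objectives in the protocol article lists "To compare the rate of acyclovir-resistant HSV between study arms". Outcome Measures turns this into "Proportion of microbiologically confirmed flares of HSV during the trial that are caused by laboratory-confirmed acyclovir-resistant HSV". Secondary Analyses repeats that definition, as "the proportion of microbiologically confirmed flares of HSV during the trial that are caused by laboratory-confirmed acyclovir-resistant HSV", and assigns it a Wilcoxon rank sum test. The definition appears in both places, so it is not a slip of wording. No resistance measure per randomised participant or per person-year is given, although the same sentence of Secondary Analyses puts adverse events and HSV reactivations on a per-year basis. That section also says that all analyses follow intention to treat.

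Three other statements bear on the measure:

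- Study Hypotheses predicts, on valacyclovir, "a lower frequency of HSV reactivations, a similar rate of acyclovir-resistant HSV".
- Background says of the chosen regimen that "the dose of 500 mg twice daily has been demonstrated to achieve excellent herpes suppression in clinical trials of HIV, HSV-2 co-infected adults".
- Management of symptomatic herpes during the trial limits what is sampled and tested. At a flare, participants are to "have samples taken to attempt microbiologic confirmation of the diagnosis where resources permit", and "If HSV resistance is suspected, specimens will be tested for acyclovir resistance using a plaque reduction assay".

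**The concern.** Treatment is expected to change the denominator of the resistance measure. A participant enters the calculation only by having a flare that is sampled and confirmed, and the trial drug is given partly to prevent flares. The ratio can therefore differ between arms because the bottom moved while the top did not.

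This is the only resistance comparison that the article lists, and resistance is the main theoretical risk it discusses for long-term valacyclovir. A higher share on active drug would be read as drug-induced resistance. A reader could not tell from the planned test whether resistant episodes had become more common or susceptible ones rarer.

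**Working it through.** The article gives no expected share, flare rate or power for this comparison, so there is no figure to reproduce. The check asks what the planned measure shows when the arms do not differ in resistant episodes per person.

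**Inputs from the article.** 240 participants per arm (Study setting). Expected follow-up 2.625 years (Sample Size Calculation). Background resistance 5-6%: "Resistance rates have stayed stable at 5-6% despite increasing population exposure to related drugs over 2 decades" (Sample Size Calculation).

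**Assumptions.** The midpoint, 5.5%, serves as the placebo-arm share p. Susceptible flares on valacyclovir are multiplied by a rate ratio RR, for which the article gives no value; the range taken is 0.20 to 1.0. Resistant flares per person are equal in the two arms.

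**Step 1: the share.** For each placebo flare, p are resistant and (1 − p) susceptible. On valacyclovir these become p and (1 − p)·RR, so the valacyclovir share is p / [p + (1 − p)·RR].

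| RR | Calculation | Share on valacyclovir |
|---|---|---|
| 1.0 | 0.055 / (0.055 + 0.945) | 5.5% |
| 0.75 | 0.055 / (0.055 + 0.70875) | 7.2% |
| 0.50 | 0.055 / (0.055 + 0.4725) | 10.4% |
| 0.25 | 0.055 / (0.055 + 0.23625) | 18.9% |
| 0.20 | 0.055 / (0.055 + 0.189) | 22.5% |

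Over p = 5% to 6% the share is 9.5% to 11.3% at RR 0.50 and 17.4% to 20.3% at RR 0.25. If resistant flares are suppressed by the same factor, the share is p·RR / [p·RR + (1 − p)·RR] = p, and there is no distortion.

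**Step 2: who has a value.** A Wilcoxon test ranks one value per participant, and a participant with no confirmed flare has 0/0. As an illustration, assume 0.5 flares per year, half of flares confirmed, and gamma-Poisson variation between participants with shape 1.

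- Placebo: mean confirmed flares 0.5 × 2.625 × 0.5 = 0.656. Proportion with at least one: 1 − 1/1.656 = 40%.
- Valacyclovir at RR 0.50: mean 0.656 × (0.055 + 0.4725) = 0.346. Proportion with at least one: 1 − 1/1.346 = 26%.

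On these assumptions most participants have no share, and those who do are selected differently in the two arms.

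**Step 3: the test.** Simulation with 240 per arm, 2.625 years, 0.5 to 2 flares per year, half of flares confirmed, every confirmed flare typed, p = 5.5% and two-sided 0.05 (1000 runs per scenario), with no true difference in resistant episodes:

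| RR | Rejection, Wilcoxon on per-participant shares |
|---|---|
| 1.0 | about 5% |
| 0.75 | 7-8% |
| 0.50 | 18-24% |
| 0.25 | 57-83% |

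At RR 0.50 and 0.25 virtually all rejections point to more resistance on valacyclovir. The same test on resistant flares counted over all 240 per arm rejects in 3.8% to 6.1% across the 12 scenarios.

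**Step 4: selective testing.** Typing every flare is generous, because the article tests only on suspicion. With half of the resistant confirmed flares tested and 0.1 to 1 flares per year, false rejection is about 1-6% at 1% resistance and RR 0.50, with under 2 detected resistant flares per arm on average. It is about 14-38% at 5.5% resistance and RR 0.25.

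**The case against.** **The objective may itself mean a share.** A reader might infer that the analysis contradicts the objective, since one speaks of a rate and the other of a proportion. The article does not support that. The objective names no denominator, and Sample Size Calculation expresses resistance rates as a percentage, so the word can mean a share here. On that reading, Study Hypotheses predicts fewer flares and a similar share, and objective, outcome and analysis agree. This stands: a contradiction is not shown. The treatment-affected denominator remains under either reading.

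**The size is not known.** The article gives no flare rate, suppression figure or expected number of resistant isolates. It says that up to 90% of people with HSV-2 have no symptoms and that resistant HSV is seen occasionally in advanced HIV, whereas this cohort enters with CD4 counts of 400-900. Few resistant isolates may be found, and a distorted share may then not reach significance: 3 of 100 flares against 3 of 30 gives a Fisher p of 0.14. This also stands. It limits how often a false signal would be declared, but not the distortion of the estimate.

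**The unit of the test is not spelled out.** The article does not say that shares are computed per participant, or how participants without a confirmed flare are handled; a fuller document may. The point about excluded participants is therefore conditional. It is nevertheless how a rank sum test on this outcome would ordinarily be run.

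**Readers can see the denominator.** Reactivations per year are compared separately, so a fall in flares would be visible. That helps interpretation but does not correct the planned comparison.

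**A per-randomised measure has its own bias.** Fewer flares mean fewer chances to sample and detect resistance. This stands and must be stated alongside the fix.

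**Conclusion.** The point holds in limited form. The only planned resistance comparison uses a post-randomisation denominator that the trial's own hypothesis expects valacyclovir to lower. It can show a higher resistant share on active drug with no difference in resistant episodes per person: 5.5% becomes 10.4% at a susceptible-flare rate ratio of 0.50. This rests on an assumed placebo share, an assumed rate ratio, and suppression acting mainly on susceptible virus. Under equal suppression the share is not distorted.

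It would be tempting to conclude that the trial will report a false safety signal, or to quote the simulated rejection rates as its error rate. Neither is supported: those rates depend on inputs that the article does not give and fall to near or below 5% when resistance is rare and testing is selective. This is one of seven secondary outcomes; the primary analysis, sample size and interim rule are unaffected.

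**What to change.** In Outcome Measures and Secondary Analyses, replace the between-arm resistance comparison with two measures over all randomised participants, each with an exact 95% confidence interval:

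1. The number of participants with at least one laboratory-confirmed acyclovir-resistant isolate, out of all randomised to each arm.
2. Resistant episodes per person-year of follow-up.

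Both are useful because follow-up ends at the primary endpoint. If valacyclovir delays that endpoint, its arm is observed for longer, and the person-year measure allows for this. Repeated episodes in one person are not independent, so the participant count should lead.

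Keep the share of confirmed flares as a descriptive companion without a test. Report it with the numbers of flares, confirmed flares and specimens tested for resistance, by arm.

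State the limitation: confirmation depends on local resources and resistance testing on suspicion, so the new measures can under-detect resistance in the arm with fewer flares and must be read with the testing counts. Rewording does not cure this.

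The cost is the rewording of one secondary outcome and its analysis, plus one descriptive table. No new data are needed.
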